## Abstract

**Background:**

Waterpipe tobacco smoking has increased among youth across the globe including in the US, and it continues as a common and traditional form of smoking tobacco in Pakistan. A range of behavioral and pharmacological therapies are available to support people in quitting cigarette smoking; however, little evidence exists for the efficacy of these therapies in achieving abstinence among waterpipe tobacco smokers. The objective of this study is to assess the efficacy of varenicline when added to behavioral support for waterpipe tobacco smoking cessation, by measuring biochemically validated continuous abstinence in waterpipe tobacco smokers.

**Methods/design:**

This is a two-arm, double-blind, placebo-controlled randomized trial conducted in four districts in Punjab, Pakistan. Study participants include adults using a waterpipe (with or without concomitant cigarette, bidi or other forms of tobacco smoking) on a daily basis for at least 6 months and who are willing to quit. We will individually randomize 510 participants to one of the two arms of the trial. Participants in the intervention arm will receive varenicline and behavioral support and those in the control arm will receive placebo and behavioral support. The primary outcome will be continuous abstinence for at least 6 months (week 25) which is biochemically verified by a carbon monoxide level of <10 ppm. Secondary outcomes will include biochemically verified 7-day point abstinence at 5, 12 and 25 weeks and any lapses and relapses between the different assessment points. Tertiary outcomes will include assessment of withdrawal symptoms using the Mood and Physical Symptoms Scale (MPSS), smoking dependency using the Lebanon Waterpipe Dependency Scale (LWDS-11) and monitoring adverse outcomes.

**Discussion:**

This is an efficacy trial and would require a subsequent effectiveness trial for a definitive evaluation of the intervention.

**Trial registration:**

ISRCTN, ISRCTN94103375. Registered on 1 December 2015.

**Electronic supplementary material:**

The online version of this article (doi:10.1186/s13063-016-1761-y) contains supplementary material, which is available to authorized users.

## Background

Waterpipe tobacco smoking, also known as hookah, Shisha or narghile, is a growing public health concern worldwide. In waterpipe tobacco smoking, tobacco is heated by burning charcoal in a stemmed, water-containing apparatus. Users inhale a mixture of tobacco and charcoal smoke by breathing in on a hose that is attached to the apparatus. One waterpipe session can last between several minutes to several hours [1]. The activity has been practiced for centuries and, while popularity has markedly increased worldwide, it remains embedded within south Asian culture, particularly in Pakistan. According to the latest Global Adult Tobacco Survey (GATS, 2014) conducted in Pakistan, 22.2% of men, 2.1% of women and 12.4% of the overall adult population currently smoke tobacco (15.6 million adults currently smoke tobacco). The same survey states that 4.7% of men, 1.1% of women and 3.0% of the overall adult population currently use a waterpipe (3.7 million adults). Furthermore, the GATS, 2014 states that about one in four smokers made an attempt to quit in the past 12 months. Despite the widely held belief that waterpipe tobacco smoking is safer than cigarette smoking [2], research has shown the contrary. The tobacco mixture contains significant levels of nicotine, known for its addictive properties, as well as tobacco-specific nitrosamines, volatile aldehydes, heavy metals and “tar,” which cause respiratory diseases and cancer [3, 4]. Tobacco-like adverse health effects from waterpipe tobacco smoking are, therefore, expected and well-documented in a recent meta-analysis, which revealed a positive association between waterpipe tobacco smoking and lung (odds ratio (OR) 4.6, 95% CI 2.6–8.0) and esophageal (OR 3.6, 95% CI 1.4–9.4) cancers [5]. As with cigarettes, nicotine dependence is a key feature of regular waterpipe tobacco smokers who exhibit cravings, withdrawal symptoms and other nicotine-modulated behaviors [6, 7].

The effectiveness of smoking-cessation strategies including behavioral support and pharmacotherapies, such as varenicline, has been well-established among cigarette smokers [8, 9]. Varenicline has also shown to be more effective and cost-effective than nicotine replacement therapy [10] and bupropion [11], respectively. In a previous study [12] behavioral support was found to be effective among hookah smokers (relative risk (RR) 2.2; 95% CI 1.3–3.8) but to a lesser extent than among cigarette smokers (RR 5.8; 95% CI 4.0–8.5). This study was a subgroup analysis of a large cluster randomized controlled trial (RCT) (Action to Stop Smoking In Suspected Tuberculosis) in Pakistan, which found 41.0% smoking abstinence in the behavioral support group compared to 8.5% in the control group [13]. Combining varenicline with behavioral support has further potential in increasing cessation success [14]. However, the efficacy of varenicline (either alone or in combination with other therapies) in waterpipe tobacco smoking cessation is currently unknown. The two RCTs to date assessing the effectiveness of smoking cessation strategies in waterpipe tobacco smokers did not evaluate varenicline [12, 15]. Moreover, these trials have either shown little or modest success in getting waterpipe tobacco smokers to quit as compared to cigarette smokers [12, 15]. This calls for further therapies, such as varenicline, to be evaluated in this population. This study will be the first to explore the efficacy of varenicline in waterpipe tobacco smoking cessation. Given the increased use of the waterpipe use across all continents and the paucity of evidence on interventions for its cessation, this study is critically important for public health and could provide a scientific breakthrough in this area. The items in this protocol comply with the recommended SPIRIT checklist (Additional file 1).

## Methods/design

### Aims and objectives

Our key aim is to assess whether varenicline coadministered with behavioral support is more efficacious in achieving 6 months’ continuous abstinence from all forms of tobacco smoking among waterpipe tobacco smokers than a combination of placebo and behavioral support. Therefore, the primary objective of the trial is to assess the efficacy of varenicline when added to behavioral support for smoking cessation, by measuring biochemically validated continuous abstinence at week 25 in waterpipe tobacco smokers. The secondary objectives are to: (1) assess the efficacy of varenicline when given with behavioral support in achieving point abstinence at week 5, week 12 and week 25, (2) compare the efficacy of varenicline when given with behavioral support in achieving point and continuous abstinences between exclusive waterpipe tobacco smokers and those who combine it with other forms of smoking tobacco, (3) assess the proportion of early and late lapses, and their ability to predict abstinent failures and (4) assess the proportion of early and late relapses and determine their predictors. In addition, we will first translate and then assess the psychometric properties of the Mood and Physical Symptoms Scale (MPSS) and the Lebanon Waterpipe Dependency Scale (LWDS-11) in the target population.

### Design

This is a two-arm, double-blind, placebo-controlled, randomized trial. Participants randomized to treatment (arm 1) will receive varenicline while those randomized to the control arm (arm 2) will receive placebo. In addition, behavioral support will be provided to participants in both arms.

### Settings

The study is being conducted in four districts (Chakwal, Khushab, MandiBahauddin, and Rawalpindi) of Punjab, Pakistan. Based in district hospitals in three districts and a teaching hospital in one district (Rawalpindi), the study will recruit participants from a large catchment population in both urban and rural settings.

### Study participants

We will recruit 510 adults who smoke a waterpipe on a daily basis for at least 6 months, with or without concomitant cigarette, bidi or other tobacco smoking and who wish to quit smoking. We define daily waterpipe tobacco smoking if a person smokes on more than 25 days in a month. We will exclude those who (1) have used any pharmacotherapy for tobacco dependence (including nicotine replacement therapy and electronic cigarettes) in the last 30 days, (2) are pregnant, lactating or planning to become pregnant, (3) have a medical condition requiring hospitalization, (4) have previously used varenicline and had an allergic reaction, (5) have a history of heart disease, including unstable angina, untreated cardiac arrhythmia, myocardial infarction, or have undergone a cardiac procedure (in the last 3 months), (6) have uncontrolled hypertension or a history of stroke, (7) have a history of chronic kidney disease, (8) have a history of epilepsy, (9) have suicidal ideation or a history of self-harm, (10) have a history of schizophrenia, psychosis or bipolar disorder, (11) have current moderate or severe depression, (12) currently use smokeless tobacco and (13) actively use substances (including alcohol misuse) other than tobacco.

The following methods will be used to identify and recruit potential participants:Recruiting hospital patients: we will provide half-day training to all health care staff in each hospital to identify potential trial participants among adult hospital attendees and refer them to a research assistant based in a respective hospital for eligibility assessmentRecruiting patients’ relatives/attendants: we will put up posters and make leaflets available in the reception hall, outpatient departments, hospital wards and other relevant departments with a brief explanation about the study and inviting participants. These will be targeted at patients as well as their attendants. Interested people will be asked to contact a respective research assistantRecruiting members of public: we will also recruit eligible and consenting individuals among catchment populations of the participating hospitals. We will advertise our trial and invite people to participate through local newspapers, local cable TV and/or using community networks. Interested people will be also identified through local connections and/or previously enrolled participants in the trial and put in contact with the research assistant. Individuals recruited via community networks will be offered trial enrollment in the community in case they are not able to visit the respective hospital site

Once identified and referred to our resident research assistant, all potential participants will be assessed for eligibility. Research assistants will be trained to go through the inclusion and exclusion criteria and make a final eligibility assessment. A screening register will be kept at each site, which will have potential participants’ “screening” number, responses to questions asked to assess eligibility and the outcome of their eligibility assessment. Those found to be eligible will be given verbal and written information about the trial and 24 h to consider participation. Potential participants will be given an opportunity to clarify anything that they do not understand and ask related questions. It will also be explained that they are free to leave the study at any point without any consequences on their routine and entitled medical treatment. Participants will not receive any financial incentives to participate in the trial except to cover their travel expenses. Written consent will be obtained by the research assistant from those interested by going through a checklist on the Consent Form and obtaining an ink signature or a thumb impression (thumb impression is officially acceptable in Pakistan for those who cannot write). The outcome on the Consent Form will also be recorded on the eligibility register. All eligible and consenting participants will be formally enrolled in the trial and a minimum set of information (sex, concomitant smoking other than waterpipe) will be obtained, necessary for randomization. Where applicable, reasons for not meeting the eligibility criteria or declining to participate will be recorded on the screening register.

Treatment can be withdrawn at any time after randomization and allocation if significant intolerance to the study treatment is suspected. Other reasons for withdrawing from study treatment are: (1) the participant makes a voluntary decision to withdraw from the study, (2) the participant has a serious clinical adverse event, develops a new medical condition or suffers from worsening of any existing illness, which indicates that continuing in the study will not be in their best interest. Study treatment will also be withdrawn if the participant develops a life-threatening or severely disabling medical condition, or requires hospitalization and (3) female participants who become pregnant or intend to become pregnant. If a participant is withdrawn from the study due to treatment intolerance or for any of the above reasons, their follow-up assessments and data collection will continue as per protocol. If the treatment is discontinued due to drug intolerance or any serious clinical adverse event, the participant will be followed up until the intolerance/event subsides and there is a return to an acceptable clinical status, ascertained by a physician.

#### Randomization and allocation

Those who consent will be randomly assigned to one of the two treatment conditions by using a computer-generated allocation sequence designed at the University of York. The system, created in software R v3.2.2, will generate a permuted block randomization list for each site with stratification factors including gender and concomitant smoking. Based on this random sequence, the system will allocate each newly recruited participant either to varenicline or to placebo treatment. For treatment allocation, the research assistant will make a phone call to the trial manager based at the central research office in Islamabad. On providing the basic information on recruiting district, gender, and concomitant smoking, the trial manager will generate a trial ID by running a prespecified code (for each random block) in the R file. At this point, both the trial manager and the research assistant will be unaware of the treatment condition associated with each trial ID. The trial ID will correspond to that on the medication packs already made available at each participating hospital. Under no circumstances will an enrolled participant be dispensed a medication pack other than the one assigned through the randomization system. To ensure double-blinding, we will use identical medication packs for both placebo and varenicline, labeled only with a unique trial ID. The investigators, research assistants and participants will be blinded to the allocation until the trial database is locked at the end of the study.

### Interventions

Once enrolled, participants in the trial will be randomized to receive behavioral support either with varenicline or with placebo.

### Behavioral support

Behavioral support will be offered to all waterpipe tobacco smokers as part of routine care. Hence, all trial participants, irrespective of their treatment condition, will receive behavioral support intervention using an educational flipbook. This will consist of two structured sessions. A 30-min session at the first visit will aim to encouraging waterpipe tobacco smokers to see themselves as nonusers and to set a plan for a quit day 1 week later. This is then followed by a 10-min session, coinciding with their quit day, to review progress. Further encouragement and support will be offered at subsequent visits in week 5.

### Varenicline

Participants allocated to the varenicline and behavioral support arm will receive their first week’s supply on the day of trial enrollment. The treatment, in the form of 0.5-mg tablets, will be dosed at 0.5 mg once daily on days 1–3 and 0.5 mg twice daily on days 4–7. Participants will be expected to return at the end of week 1, coinciding with their quit day, at which point they will be dispensed another pack of medication for 11 weeks, with the pill in the form of 1-mg tablets to be taken twice daily for the rest of the treatment duration. Adherence will be monitored at each visit by using a 7-day timeline follow-back and by looking at the tablets left in the bottle. A 7-day timeline follow-back will consist of a set of questions administered at weeks 1, 5 and 12 asking participants if they have taken the prescribed treatment in the previous week by recalling each day of the week. Adherence will be considered “complete” if the participant adheres throughout 12 weeks; and “partial” if adherence is either irregular or not for the entire period. Participants will be asked to record the nature, timing and duration of any adverse events (AEs) with clear guidance on when to stop the medication and when, and how, to report back to the named clinician in the participating hospital. These clinicians would have received the basic training required in this regard.

### Placebo

By virtue of being a double-blind trial, participants allocated to the placebo and behavioral support arm will be dispensed placebo in exactly the same manner as described above for varenicline, i.e., a pack of 0.5-mg tablets in the first week and a 1-mg pack for the following 11 weeks.

Pfizer is responsible for ensuring that the quality and quantity of the study treatment is adequate for the trial. All treatment packs were shipped to the central research office in Islamabad and the trial manager is responsible for storing these at room temperature. An independent researcher was employed to give the treatment packs their allocation IDs. A list of these trial IDs will be forwarded to the trial statistician who will feed this into the computer program that will generate a random allocation sequence. The treatment packs will then be given out to each hospital where these will be stored in a locked cupboard at room temperature within the hospital pharmacy. Although medication packs will not disclose the treatment condition, their labels will contain the following information: (1) LOT number given by Pfizer, (2) unique trial ID given by an independent researcher, (3) principle investigator’s details, (4) sponsor’s details, (5) hospital address, (6) expiry date, (7) patient’s name and (8) directions for use. Each pack will also clearly say “For use in Hookah Trial only.” A treatment supply register will be kept both at the hospital as well as at the central research office. All left-over treatment packs will be returned from the participating hospital sites to the central research office and will be disposed off after completion of the trial follow-ups.

### Primary outcome

As per Russell’s Standard [16], the primary outcome will be self-reported continuous abstinence for at least 6 months (no smoking allowed in the 7 days prior to each of the three assessments) which is biochemically verified by a carbon monoxide (CO) level of <10 ppm measured by Micro CO (Micro Medical Ltd., Rochester, United Kingdom) at week 5, week 12 and week 25. When a participant self-reports abstinence with an elevated CO level of >10 ppm on any of the three assessments, we will use urinary kits for checking cotinine levels in such cases. Depending on the cotinine level findings the participant will be categorized as a smoker or not.

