### Secondary outcomes

Based on the combination of self-report and CO levels, these will include:Point abstinence, defined as a self-report of not smoking in the previous 7 days and verified by a CO level of <10 ppm, at week 5, week 12 and week 25Early lapse, defined by a self-report of smoking (even once) after the quit date but having point abstinence at week 5Late lapse, defined by a self-report of smoking (even once) between week 5 and week 12 but showing point abstinence at week 5 and week 12Early relapse, defined by point abstinence at week 5 but a smoking status in later assessmentsLate relapse, defined by point abstinence at week 5 and week 12 but a smoking status at week 25Differences in the point and continuous abstinences, lapses and relapses between exclusive waterpipe smokers and those who combine it with other forms of smoking tobacco

We will also translate the MPSS [17] for use in a Pakistani population. Once translated, the scale will be administered at baseline and week 25. The scale assesses withdrawal symptoms including anxiety, depression, irritability, restlessness, hunger, concentration and sleep. It also assesses the frequency and strength of urges to smoke. As above, we will also translate the LWDS-11, a tobacco-dependence measure [7], to be administered at baseline and week 25. The scale consists of 11 items and four subscales, the first representing nicotine dependence, the second negative reinforcement, the third psychological craving and the fourth positive reinforcement.

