### Data collection and management (Fig. 1)

**Fig. 1 Fig1:**
[figure not shown]
CONSORT Flow Diagram

All participants will undergo a baseline assessment including demographic variables (e.g., age, sex, ethnicity, socioeconomic status), past and present smoking (all forms), motivation to quit, withdrawal symptoms (MPSS) and dependency assessments (LWDS-11). Information on waterpipe use will also be collected which will include the quantity, duration and frequency of waterpipe tobacco smoked at the baseline. We will also enquire about their knowledge of health risks associated with waterpipe tobacco smoking, attitudes towards waterpipe tobacco smoking, and intention to quit. The use of concomitant medications will also be collected at baseline. Although social support is not directly assessed, whether smoking is permitted inside the home is assessed. Further assessments at weeks 5, 12 and 25 will include current smoking, any changes in smoking patterns, medication-related AEs and CO breath tests. MPSS, LWDS-11, Strength of Urges to Smoke (SUTS) and cotinine urine tests will be carried out at week 25 (Fig. 2). To pay for their travel and subsistence expenses, participants will receive 200 Pakistani Rupees (approximately US$2) at the last follow-up. Those failing to attend will be reminded and asked to at least send their smoking status via text (mobile phone coverage is high in Pakistan). Where possible, a home visit will be arranged to perform CO measurements. In our previous experience of conducting smoking-cessation trials in Pakistan, such strategies have been successful in keeping attrition rates below 10% [13]. Data will still be collected and maintained on those who either discontinue or deviate from treatment protocols to assess fidelity to the treatment. Data will be initially collected in the form of paper-based questionnaires. Containing no participant-identifiable information, these will be kept in a locked cupboard separate from the Consent Forms at the participating hospital. Every week, these will be photocopied and sent over to the central research office through a secure courier service. Once received, data will be entered in a secure trial database managed by the University of York, created using Qualtrics software (Qualtrics, Provo, UT, USA). Paper copies will also be kept secure in a locked cupboard.

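### Cotinine can overrule a raised CO for the primary outcome but not for point abstinence, so a participant can be continuously abstinent yet fail week-25 point abstinence

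*Protocol article*

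**What the plan says.** Protocol article, Primary outcome. Self-reported abstinence is "biochemically verified by a carbon monoxide (CO) level of <10 ppm measured by Micro CO" at weeks 5, 12 and 25. A second step follows: "When a participant self-reports abstinence with an elevated CO level of >10 ppm on any of the three assessments, we will use urinary kits". The outcome of that step is decisive: "Depending on the cotinine level findings the participant will be categorized as a smoker or not".

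Protocol article, Secondary outcomes. The list opens "Based on the combination of self-report and CO levels, these will include", and point abstinence is "a self-report of not smoking in the previous 7 days and verified by a CO level of <10 ppm". Cotinine is not mentioned. Early lapse and early relapse require point abstinence at week 5; late lapse and late relapse require it at weeks 5 and 12. Both relapse definitions also use the term *smoking status*, which the section does not define.

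Protocol article, Data collection and management. "Further assessments at weeks 5, 12 and 25 will include current smoking, any changes in smoking patterns, medication-related AEs and CO breath tests". Cotinine appears in the next sentence: "cotinine urine tests will be carried out at week 25".

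**The concern.** Continuous abstinence through week 25 should imply point abstinence at week 25. It does so only if both outcomes verify abstinence in the same way, and here they do not: one allows cotinine to overrule CO and the other does not. This goes beyond detail left out of an article, because the Secondary outcomes section states a rule of its own that differs from the primary one.

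What is at stake is mainly the secondary classification. Point abstinence at three visits, lapse and relapse are all built on the CO-only rule. The Statistical analysis section analyses point abstinence and lapse formally, and compares point and continuous abstinence between exclusive waterpipe smokers and those with concomitant smoking. The secondary objectives ask how often lapses and relapses occur and what predicts them.

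**Working it through.** **1. Truth table.** Take a participant who reports abstinence at every visit and has CO <10 ppm at weeks 5 and 12. Apply the two sections literally at week 25.

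| Week-25 CO | Cotinine | Primary outcome | Week-25 point abstinence |
|---|---|---|---|
| <10 ppm | any | success | yes |
| >10 ppm | positive | failure | no |
| >10 ppm | negative | **success** | **no** |
| exactly 10 ppm | any | not verified, and not sent to cotinine | no |

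The third row is the contradiction. The fourth is a gap: a reading of 10 ppm gets no cotinine test, although a higher reading does.

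**2. Cleared by cotinine at week 5.** For the primary outcome this participant counts as a non-smoker at week 5. For the secondary outcomes the participant is not point abstinent at week 5, and so can enter none of the four lapse and relapse categories:
- The primary outcome forbids smoking only in the 7 days before each assessment. A primary success may therefore have smoked between the quit date and week 5, yet would not be counted as an early lapse.
- If the participant resumes smoking later, no relapse is recorded.

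This result does not depend on what *smoking status* means.

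**3. The plan's own figure.** Inputs from the Sample size section: 37% control, a 13-point difference (so 50%), 80% power, 5% significance (taken as two-sided), equal arms (assumed), 10% dropout. With pooled variance and no continuity correction:

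n = [1.960·√(2·0.435·0.565) + 0.842·√(0.37·0.63 + 0.50·0.50)]² / 0.13² = 227.1, so 228 per arm.

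Dropout: 228/0.9 = 253.3, so 254 per arm and 508 in total. Both stated figures reproduce, and nothing in this point changes them.

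**4. Illustration of size.** The document does not say how often a self-reported abstainer has raised CO with negative cotinine. Let f be that share among expected successes at one visit, and take 37% and 50% as the cotinine-adjudicated rates. Expected successes among 456 analysed: 228·0.37 + 228·0.50 = 84.4 + 114.0 = 198.4.

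| f (assumed) | Classified differently (198.4·f) | CO-only rates | Risk ratio | Power, CO-only, 228 per arm |
|---|---|---|---|---|
| 0 | 0 | 37.0% vs 50.0% | 1.35 | 80% |
| 2% | 4.0 | 36.3% vs 49.0% | 1.35 | 79% |
| 5% | 9.9 | 35.1% vs 47.5% | 1.35 | 77% |
| 10% | 19.8 | 33.3% vs 45.0% | 1.35 | 73% |

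The risk ratio is constant because the same factor (1 − f) multiplies both arms. The last column applies only if the primary outcome itself were scored on CO alone.

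**The case against.** The strongest reply is that each section governs its own outcome. The primary rule is stated, the sample size does not depend on this issue, and the remedy is a short clarification of the secondary outcomes. Most of that stands, and it limits how serious the point is. It does not remove the contradiction, because two outcomes that should be nested are not, and no other part of the article reconciles them.

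A reader might also infer more than the document supports:

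- **That the week-25 participant is also a late relapse.** This depends on *smoking status*, which is undefined. If it is read on self-report and CO, as the opening of the Secondary outcomes section suggests, the participant is a late relapse. If the cotinine classification in the Primary outcome section is carried over, the participant is not. The text does not decide between them.
- **That cotinine cannot be done at weeks 5 and 12.** The Data collection section lists it at week 25 but does not say only then. It may mean routine testing at week 25 in addition to conditional kits at the earlier visits, and the schedule in Fig. 2 is not available here. The mismatch may be only apparent.
- **That cotinine ought to work in both directions.** Using it only to adjudicate a raised CO is a design choice. How a positive week-25 cotinine with CO <10 ppm is handled, and the kit's cut-off, may be set in the full protocol or SAP.
- **That 4–22 participants are affected.** That range comes from applying 2–10% to 255·0.37 + 255·0.50 = 221.9 successes and counting everyone with raised CO. Those with positive cotinine fail under both rules, so it is an upper bound, and it ignores the planned 10% dropout.

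On the 10 ppm gap, it can fairly be said that such a reading simply fails the <10 ppm test. That is the likely default, but it denies the participant the adjudication that a higher reading receives.

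**Conclusion.** The stated rules conflict and should be reconciled. A participant cleared by cotinine at week 25 is continuously abstinent but not point abstinent, and one cleared at week 5 drops out of every lapse and relapse definition. These two results follow from the text alone.

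The size cannot be derived from the document. Under an assumed 2–10% of expected successes with raised CO and negative cotinine at one visit, about 4–20 of 456 analysed participants would be classified differently. Because classification is blinded, there is no evident reason for the rate to differ by arm. With equal rates the risk ratio is essentially unchanged, and 228 per arm and 508 in total stand. This is an error in the outcome definitions that mainly affects secondary classifications. It is not evidence of bias in the primary comparison.

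**What to change.** Write one verification rule and apply it to the primary outcome, point abstinence, lapse and relapse at weeks 5, 12 and 25: self-reported abstinence with CO <10 ppm is verified; self-reported abstinence with CO ≥10 ppm goes to urinary cotinine, which decides. Define *smoking status* in the relapse definitions by the same rule. State in Data collection and management that conditional cotinine testing applies at all three visits, separately from any routine testing at week 25. Report a sensitivity analysis that scores abstinence on CO alone.

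The cost is a few lines of protocol wording, one additional analysis, and urine kits for a small group at weeks 5 and 12 that the Primary outcome section already implies. The sample size does not change. The rule should be fixed before outcomes are classified.
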